### 2.2. Sample

We will assemble a wide-ranging and reliable sample, using a semi-randomized controlled experimental study, ensuring that our methodology is implemented. For the experimental study to produce reliable results, 39 participants will be involved, each with specific selected characteristics (Table 2). To ensure we have enough participants for our study, we used G*Power (version 3.1.9.6—software designed by the University of Kiel, Germany). Our study required a two-tailed test, with an alpha level of 0.05, power of 90%, and an effect size (d) of 1.39, which were taken into consideration during the design of our study [27,28].

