## Abstract

The benefits of Pilates have been extensively researched for their impact on muscular, psychological, and cardiac health, as well as body composition, among other aspects. This study aims to investigate the influence of the Pilates method on the learning process, motor control, and neuromuscular trunk stabilization, specifically in both experienced and inexperienced practitioners. This semi-randomized controlled trial compares the level of experience among 36 Pilates practitioners in terms of motor control and learning of two Pilates-based skills: standing plank and side crisscross. Data will be collected using various assessment methods, including abdominal wall muscle ultrasound (AWMUS), shear wave elastography (SWE), gaze behavior (GA) assessment, electroencephalography (EEG), and video motion. Significant intra- and inter-individual variations are expected, due to the diverse morphological and psychomotor profiles in the sample. The adoption of both linear and non-linear analyses will provide a comprehensive evaluation of how neuromuscular structures evolve over time and space, offering both quantitative and qualitative insights. Non-linear analysis is expected to reveal higher entropy in the expert group compared to non-experts, signifying greater complexity in their motor control. In terms of stability, experts are likely to exhibit higher Lyapunov exponent values, indicating enhanced stability and coordination, along with lower Hurst exponent values. In elastography, experienced practitioners are expected to display higher transversus abdominis (TrA) muscle elasticity, due to their proficiency. Concerning GA, non-experts are expected to demonstrate more saccades, focus on more Areas of Interest (AOIs), and shorter fixation times, as experts are presumed to have more efficient gaze control. In EEG, we anticipate higher theta wave values in the non-expert group compared to the expert group. These expectations draw from similar studies in elastography and correlated research in eye tracking and EEG. They are consistent with the principles of the Pilates Method and other scientific knowledge in related techniques.

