#### Eligibility Criteria

The sample for the experienced group will be selected from a local Pilates studio. Participants must have more than six months of practice, with more than 1 h of practice per week [27]. The non-expert group will be composed of subjects who must not have had any Pilates practice in the last three months. For the control group, in addition to not practicing any form of Pilates in the last three months, we also require that they not practice any form of Pilates during the study. These subjects will be allowed to maintain their physical activity routines or create new routines if body and mind activities are not included (yoga, body balance, tai-chi, among others). All groups will be composed of 13 participants between 30 and 50 years of age. The exclusion criteria are pregnancy and medical contraindications to practicing physical exercise [29].

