### 2.6. Statistical Analyses

This study seeks to contribute to the explanation and understanding of phenomena related to Pilates using a mixed quantitative and qualitative methodology. For the statistical treatment and linear analysis, IBM SPSS Statistics 28.0 software (IBM Corporation, New York, NY, USA) will be used, with a level of significance at 5% (*p* < 0.05). Descriptive statistics, including the calculation and analysis of the mean and standard deviation, will be conducted for all variables. If validation of the normality and heterogeneity assumptions of the sample are assured, then the analysis of variance ANOVA [56] will be used with multiple comparisons of means performed using the post-hoc Tukey test to verify the differences between the groups [57]. The effect size (ES) for ANOVA test is interpreted using the following criteria: no effect (ES < 0.04), minimum effect (0.04 ≤ ES < 0.25), moderate effect (0.25 ≤ ES < 0.64), and strong effect (ES ≥ 0.64) [58]. Apart from the effect size, the power (π) of the corresponding test will also be presented [59]. Pearson’s correlation analysis is defined to establish the associations between the studied variables [60].

While linear measures are useful for quantitative data analysis, taking a different perspective, non-linear data analysis is employed to characterize the collected data. This type of analysis provides insights into the organization of data within a system, offering a more nuanced understanding of the underlying patterns and structures in the dataset. The regularity, variability and complexity of the signal and the motor system in different levels of response [61,62] can lead to a larger understanding of the collected data. In fact, sample entropy can tell the amount of uncertainty attending the order of an output signal, i.e., predictability [63]. On the other hand, the Lyapunov exponent will be used to analyze the periodicity and regularity of the signal and the motor system in a time series [61]. Finally, the Hurst exponent [64,65] will be used to measure the tendency of the values of the motor system along a time scale. To proceed with the computation of the time series, the program will use UPATO [66].

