**Figure 3 healthcare-12-00229-f003:**
[figure not shown]
Figure of marker set placement (adapted from ROBOCORP Laboratory; the image does not require a copyright).

**Table 1 healthcare-12-00229-t001:** Study variables.

Dependent Variables							
			AWMUS + SWE	EEG	GAZE	QUALI	Video *
Independent Variables	Level of experience in Pilates	Control group	S1	S2	S3	S4	-
		Non-expertise group					
		Expertise group					
	Mirror	Mirror image	S1	S2	-	S4	-
		No mirror image					
	DEXA *		-	-	-	-	-

Legend: S1—study 1; S2—study 2; S3—study 1; S4—study 4; ECO—Abdominal Wall Muscle Ultrasound (AWMUS); SWE—Shear Wave Elastography; EEG—Electroencephalography; GAZE—Gaze behavior Assessment; QUALI—Qualitative research; DEXA—Dual-energy X-ray Absorptiometry. * Correlated variables—Used to establish analysis and identification correlations with other variables.

**Table 2 healthcare-12-00229-t002:** Sample operationalization and descriptive data.

Topic	Description	Operationalization	
Age	Age range between 30 and 50 years old		No pathologies that make physical practice unfeasible (according to RGPD and DL nº5/2007)
Gender	Gender Balance (approximately 20 males and 20 females)		
Experience level	Expertise	Practitioners who attend Pilates sessions in one of its forms, for more than 6 months with a frequency equal to or greater than two weekly workouts lasting between 45 and 60 min [27]	
	Non-expert	Practitioners who have never performed Pilates sessions in any of its forms or subjects who have performed Pilates for less than 3 months for more than a year will also be admitted to this group [27].	
Health condition		Unhealthy subjects will not participate in the study according to Portuguese law. The following will exclude participants from the sample: glaucoma, epilepsy, or pregnancy [27]	

**Table 3 healthcare-12-00229-t003:** Markers of anatomical assessment for each muscle [13,31].

Muscle	Anatomical Marker
RA	Measurements on the right side only Probe: Vertical Zone: 10 cm to the left of the umbilical scar at the midpoint between the iliac crest and the last rib
EO	
OI	
TrA	Measurements on the right side only Probe: Horizontal Zone: At the level of the navel and 2 cm to the right of the mid-axillary line

**Table 4 healthcare-12-00229-t004:** Markers of anatomical assessment for each muscle.

Marker Name	Location
RALH	Approximately over the temple and preferably aligned with the lateral commissure of the eye
LALH	

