RPLH	Over the Occipital bone and at the same level as RALH and LALH on the frontal and sagittal plane
LPLH	
RAC	Acromial edge of the scapula
LAC	
C7	7th Cervical Vertebrae
IJ	Jugular Insertion/Notch of the Sternum
PX	Xiphoid Process of the Sternum
RLELB	Lateral Epicondyle of the Humerus
LLELB	
RMELB	Medial Epicondyle of the Humerus
LMELB	
RRAD	Radio-Styloid Process
LRAD	
RULN	Ulna-Styloid Process
LULN	
RLH	Lateral portion of the 5th metatarsal head
LLH	
RMH	Medial portion of the 5th metatarsal head
LMH	
RASIS	Anterior Superior Iliac Spine
LASIS	
RPSIS	Posterior Superior Iliac Spine
LPSIS	
RTROC	Trochanter
LTROC	
RLK	Lateral Condyle of the Femur
LLK	
RMK	Medial Condyle of the Femur
LMK	
RFAX	Proximal tip of the head of the Fibula
LFAX	
RTTC	Most anterior portion of the Tibia Tuberosity
LTTC	
RLA	Lateral prominence of the lateral Malleolus
LLA	
RMA	Medial prominence of the lateral Malleolus
LMA	
RCA	Distal end of the posterior aspect of the Calcaneus. Should be vertically aligned with FM2.
LCA	
RFM1	Lateral aspect of the 1st metatarsal head
LFM1	
RFM2	Dorsal aspect of the 2nd metatarsal head.
LFM2	Calcaneus marker should be vertically aligned.
RFM5	Lateral aspect of the 5th metatarsal head
LFM5	

**Table 5 healthcare-12-00229-t005:** Timetable for each task included in the project.

Stage	Estimated Dates	Interviewers	Output
Project submission to the Ethics Committee (EC)	September 2022	PhD student	Project and fill out the EC form
Pilot experiment	February 2023	PhD student/small sample/18 volunteers	Published 1 study (pilot experiment)
Presentation of the Project to the Scientific Council (CC) of FCDEF	October 2023	PhD student	Project
Experiment	September 2024	PhD student/large sample/27 volunteers	1–2 published articles

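### The planned total is given as 36, 39 and 27, and the 90% power appears to belong to a two-group t-test rather than to the planned three-group Tukey comparisons

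*Protocol article*

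**What the plan says.** **Sample size.** The abstract says that the trial "compares the level of experience among 36 Pilates practitioners". Section 2.2 says that "39 participants will be involved". The eligibility text agrees with section 2.2: "All groups will be composed of 13 participants between 30 and 50 years of age", and there are three groups (expert, non-expert, control). In Table 5, the row for the main experiment reads "PhD student/large sample/27 volunteers". The pilot has its own row, with 18 volunteers. Table 2 adds a sex-balance target: "Gender Balance (approximately 20 males and 20 females".

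**Power.** Section 2.2 says "we used G*Power (version 3.1.9.6" and gives the inputs: "Our study required a two-tailed test, with an alpha level of 0.05, power of 90%, and an effect size (d) of 1.39". It names no test and no resulting number per group.

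**Analysis.** Section 2.6 plans, at the 5% level, an ANOVA with "multiple comparisons of means performed using the post-hoc Tukey test to verify the differences between the groups".

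**The concern.** There are two linked problems.

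First, three different totals describe the same planned study. No dropout allowance, pooling with the pilot or evaluable subset is stated that would connect them. As written, a final enrolment of 27, 36 or 39 could each be reported as the planned size.

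Second, the power inputs describe a comparison of two groups: Cohen's d is a two-group effect size, and an ANOVA F test has no tails. The planned pairwise comparisons carry Tukey's adjustment for three groups, which raises the critical value and lowers the power. The 90% is the only quantitative support for the sample size, so it should belong to a comparison that will be made and to a single stated number of participants.

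**Working it through.** **Inputs.** d = 1.39, two-sided alpha 0.05 and power 90% (section 2.2). Three equal groups of 13 (eligibility text). The abstract's 36 is taken as 3 × 12. Table 5's 27 is taken as 3 × 9; the equal split is an assumption, because Table 5 gives no group sizes. Equal standard deviations are assumed throughout.

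**Step 1: reproduce the stated power.** For a two-sample t-test with n per group, df = 2n − 2 and the noncentrality is d × √(n/2).

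- n = 11: power 87.3%
- n = 12: noncentrality 1.39 × √6 = 3.40, power 90.2%
- n = 13: noncentrality 1.39 × √6.5 = 3.54, power 92.5%

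The smallest n reaching 90% is 12 per group, and 3 × 12 = 36 matches the abstract. The calculation is therefore correct for the test that it appears to use. Other variants fit less well: a one-sided test needs 10 per group and a paired test 8 in total.

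**Step 2: power for one Tukey pair.** The noncentrality is unchanged. With the variance pooled over three groups, df = 3(n − 1), and the critical value is q(0.95; 3, df)/√2. This is 2.444 at n = 13, 2.454 at n = 12 and 2.497 at n = 9, against about 2.03 to 2.06 unadjusted on the same degrees of freedom.

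**Step 3: power for the omnibus F test.** The third mean is not given, so two scenarios are shown for a largest difference of d.

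- Evenly spaced means (0, d/2, d): f = d/√6 = 0.567.
- One group differs (0, 0, d): f = d × √2/3 = 0.655.

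**Results at d = 1.39**

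| Per group (total) | Two-sample t-test | One Tukey pair | Omnibus F, evenly spaced | Omnibus F, one group differs |
|---|---|---|---|---|
| 13 (39) | 92.5% | 85.8% | 87.0% | 94.9% |
| 12 (36) | 90.2% | 82.3% | 83.7% | 93.0% |
| 9 (27) | 79.0% | 67.4% | 69.7% | 82.4% |

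A simulation with 200,000 runs per scenario agrees with the Tukey and F columns to within about 0.2 percentage points.

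**Step 4: what would give 90% for a Tukey pair.** At 13 per group, d would have to be about 1.48. At d = 1.39, 14 per group gives 88.7% and 15 per group (45 in total) gives 91.1%.

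**The case against.** **The t-test is inferred.** Section 2.2 does not name it. That is right, and the point should be put as an inference. It is a strong one, because the wording fits a two-group test and the result reproduces the abstract's total exactly.

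**The ANOVA comes first.** A reader might infer that the 90% fails for everything planned at every stated size. The documents do not support that. Section 2.6 plans an ANOVA with Tukey as the follow-up. At 36 or 39 the omnibus test has between 84% and 95% power, depending on a third mean that the article does not give. The shortfall at those sizes is established only for a Tukey pair.

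**The explicit figure is 39.** Section 2.2 and the eligibility text agree with each other, and at that size the Tukey shortfall is about 4 points. This stands: at 39 the mismatch is modest. A reader might infer a one-in-three chance of missing the effect, but that requires 27 to be the real target and to be split equally. Table 5 is a timetable with estimated dates. It does not say how the 27 relate to the 18 pilot volunteers, although 18 + 27 = 45.

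**Table 2 is not a further conflict.** Its sex-balance row might be read as a fourth total of 40. It is an approximate target and is compatible with 39.

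**The outcome and pair behind d.** Section 2.2 cites sources for its inputs, and a condensed article may leave such detail to the full protocol. Its absence is at most secondary.

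**Conclusion.** The point holds in this form. The totals 36, 39 and 27 are not reconciled anywhere in the article, and this does not depend on any inference about the test. The stated 90% fits a two-sample t-test at 12 per group; it is not the power of the Tukey comparisons that section 2.6 plans. For one such pair at d = 1.39 the shortfall is about 4 points at 39 (85.8%), about 8 points at 36 (82.3%) and about 23 points at 27 (67.4%, assuming three groups of 9). At 27 neither the unadjusted t-test (79.0%) nor the F test in either scenario (69.7% to 82.4%) reaches 90%.

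The conclusion does not extend to the omnibus ANOVA at 36 or 39, and it does not show that the original calculation was wrong for its own test. The figures assume equal group sizes, equal standard deviations and normal data.

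**What to change.** 1. State one total in the abstract, section 2.2 and Table 5. If 27 and 18 are parts of a larger number, or if 39 includes an allowance for dropout, say so.
2. Name the test behind the G*Power calculation and give its result per group.
3. Restate the power for the planned comparison. For example: 13 per group gives 86% power for a Tukey-adjusted pairwise difference of d = 1.39, or 90% for d of about 1.48.
4. As an alternative to item 3, pre-specify one primary pairwise contrast, tested at unadjusted two-sided 5%, and keep Tukey for the remaining comparisons. The existing calculation then stands: 90.2% at 36 and 92.5% at 39.
5. If 27 is the real target, state the lower power that goes with it.

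The cost is a change of text. No extra enrolment is needed, provided that the sponsor accepts stating a power below 90% for Tukey pairs or names one primary contrast.

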#### Eligibility Criteria

The sample for the experienced group will be selected from a local Pilates studio. Participants must have more than six months of practice, with more than 1 h of practice per week [27]. The non-expert group will be composed of subjects who must not have had any Pilates practice in the last three months. For the control group, in addition to not practicing any form of Pilates in the last three months, we also require that they not practice any form of Pilates during the study. These subjects will be allowed to maintain their physical activity routines or create new routines if body and mind activities are not included (yoga, body balance, tai-chi, among others). All groups will be composed of 13 participants between 30 and 50 years of age. The exclusion criteria are pregnancy and medical contraindications to practicing physical exercise [29].

### 2.3. Intervention

The expert group will maintain their normal Pilates activity (at least once per week/60 min) in their usual facilities. The only addition to their regular routines will be the two Pilates skills (standing plank and the side crisscross) introduced and evaluated in our studies. All instructors involved in these facilities will have specific training to be able to teach and supervise these two new skills (four hours).

These two exercises will be performed in a type of sliding machine called a Standing Machine; participants will be able to perform the exercises in various positions, adding some instability, but particularly in orthostasis. In the plank, participants maintain a straight back and then flex and extend the feet for eight cycles (Appendix C—Table A2). In the side crisscross exercise, the participant maintains a lateral position while a crossing of limbs is done repeatedly for fifteen cycles (Appendix C—Table A3). The Standing Machine is patented pending number No 118908 in National Institute of Industrial Property.

All instructors will have POLESTAR^®^ Pilates training completed between 2011 and 2015. The non-expert group will start a weekly program in one of the Pilates studios participating in this study. This group has a weekly standardized session (55 min average) according to Appendix B—Table A1. These participants perform two laps around the circuit, performing 8 to 10 repetitions in each station, performing the standing plank on the first lap and the side crisscross on the second.

### 2.4. Outcomes

The outcomes associated with this project are relative to each study. They are briefly described below, despite being subject to detailed methodological protocols in each study.

#### 2.4.1. Abdominal Wall Muscle Ultrasound (AWMUS)

The ultrasound study will collect data regarding RA, IO, EO, and TrA thicknesses [30]. Based on the anatomical assessment markers for each muscle, as presented in Table 3, data will be collected on the right side of the participants’ trunks both at the initial assessment and after twelve weeks of intervention. Participants lay in the supine position with their arms extended along their torso. Data will be collected in millimeters after 3 measures on the left side of the body between superficial and deeper borders of muscles to ensure the quality of measurements [31]. The mean values will be calculated to obtain a final value for each muscle in each condition. Images of the EO, IO, and TrA muscles were obtained with the transducer positioned vertically to the participant’s trunk, ten centimeters to the left of the navel, at the midpoint between the iliac crest and the last rib [32]. In the RA muscle, the transducer will be positioned horizontally right above the navel [31]. A portable ultrasound (Acuson P500) with a transducer (Siemens Healthcare GmbH, Erlangen, Germany) will be operated by one experienced researcher (>10 years). The collections will be made (a) during rest and while performing the abdominal hollowing maneuver (AHM), and (b) during a standing plank with arms back at the end of 8 repetitions.

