## Appendix B

**Table A1 healthcare-12-00229-t0A1:** Table for planned exercises in intervention classes.

Exercise	Time Distribution		
	1–4 Week	5–6 Week	7–8 Week
Standing Leg Pump (Chair)	√	√	√
Front and Oblique Reverse Abdominals (Reformer)	√	√	√ (added yellow spring)
Bridging (Mat)	--	√	√
Footwork (Reformer)	√	√	√
Side Sit Up (Ladder Barrel)	√	√	√
Adapted Leg Pull Front (Mat)	√	√	√
Rolldown Series (Cadillac)	√ (small yellow springs)	√ (long yellow springs)	√ (long yellow springs)
Standing Plank (Standing Machine) (8 rep 2 series at first lap of circuit)	√	√	√
Side Criss Cross (Standing Machine) (8 rep 2 series at second lap of circuit)	√	√	√

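### The follow-up ultrasound is set after twelve weeks of intervention, but the non-expert programme in Table A1 ends at week 8

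*Protocol article*

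**What the plan says.** Section 2.4.1 (Abdominal Wall Muscle Ultrasound) collects muscle thickness "both at the initial assessment and after twelve weeks of intervention". This is the only follow-up time that the article states for any outcome.

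Section 2.3 (Intervention) describes the non-expert programme by reference to the appendix: "This group has a weekly standardized session (55 min average) according to Appendix B—Table A1". Table A1 in Appendix B lists the exercises under three time columns: weeks 1–4, 5–6 and 7–8. The content changes between columns: bridging enters at week 5, the rolldown springs change at week 5, and a spring is added to one reformer exercise at week 7.

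On repetitions of the two tested skills:

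- Section 2.3, describing the plank: "flex and extend the feet for eight cycles".
- Section 2.3, describing the side crisscross: "a crossing of limbs is done repeatedly for fifteen cycles".
- Section 2.3, describing the non-expert circuit: "performing 8 to 10 repetitions in each station", with the plank on the first lap and the side crisscross on the second.
- Table A1: "Standing Plank (Standing Machine) (8 rep 2 series at first lap of circuit" and "Side Criss Cross (Standing Machine) (8 rep 2 series at second lap of circuit".

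**The concern.** The study asks how Pilates affects learning, motor control and trunk stabilization, and the Results section expects differences within a group over time as well as between groups. For the non-expert group, any such change is attributed to a defined block of training, so the length of that block and its distance from the follow-up measurement are part of what is being estimated.

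Two sections give incompatible lengths. A reader running the study from 2.4.1 would train for twelve weeks without written content for the last four. A reader running it from Table A1 would stop at week 8 and then have to choose when to measure. A measurement taken as training ends and one taken after an untrained interval answer different questions, and no later analysis can turn one into the other. If sites or instructors resolve the conflict differently, the exposure will also vary within the group.

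**Working it through.** **Inputs**

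| Quantity | Value | Source |
|---|---|---|
| Intervention before follow-up ultrasound | 12 weeks | 2.4.1 |
| Programme blocks | weeks 1–4, 5–6, 7–8 | Appendix B, Table A1 |
| Session frequency, non-expert group | 1 per week | 2.3 |
| Side crisscross per session | 2 series of 8 | Table A1 |
| Repetitions per station | 8 to 10 | 2.3 |

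**Step 1: programme length.** Table A1 covers 4 + 2 + 2 = 8 weeks. The 12 weeks of 2.4.1 cannot be reproduced from it. The shortfall is 12 − 8 = 4 weeks, and 4 / 12 = 33% of the stated intervention has no programme content.

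**Step 2: is the gap closed elsewhere?** Section 2.3 gives frequency and session length but no number of weeks. The timetable (Table 5) gives project dates but no intervention length. The laboratory tables in Appendix C describe a visit, not the training period. No section mentions weeks 9–12 or a retention interval. Because the table is progressive, it is not self-evident that the last column simply continues.

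**Step 3: size in sessions and repetitions.** At one session a week, the two lengths give 8 or 12 sessions. With Table A1's content held fixed at 2 × 8 = 16 side crisscross repetitions per session:

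- 8 weeks: 16 × 8 = 128
- 12 weeks: 16 × 12 = 192
- ratio: 192 / 128 = 1.5

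The plank has the same entry in Table A1, so its totals are also 128 or 192. The ratio comes wholly from the duration conflict.

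**Step 4: are the repetition statements in conflict as well?** The eight and fifteen cycles in 2.3 are referenced to Tables A2 and A3, which are headed as laboratory protocol, and the eight matches the 8 plank repetitions at which 2.4.1 takes its ultrasound image. They are probably the test counts. However, the sentences stand under Intervention, and Tables A2 and A3 give no counts that would confirm it. For training, Table A1's 8 lies inside the 8 to 10 of 2.3. What remains open is whether the two series double the count on that lap, or mean something else, such as one series per side for the crisscross.

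**The case against.** The strongest reply is that this is one mismatch in a condensed article. Section 2.4 says that its outcome descriptions are brief and that each study has its own detailed methods. The twelve-week figure appears only under the thickness ultrasound. Comparisons at the initial assessment, where both exercises are meant to be new to everyone, do not depend on programme length. All of that stands and limits the reach of the point. It does not remove it: condensing can explain an omitted figure, but not two stated figures that disagree.

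A reader might also infer more than the documents support:

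- **That the intervention is undefined.** It is not. Exercises, equipment, progression, weekly frequency and session length are given for weeks 1–8.
- **That planned crisscross practice varies threefold, from 64 to 192.** The lower figure (8 × 8) takes Table A1's length but drops its two series; the upper (16 × 12) keeps them. Held to Table A1's content, the range is 128 to 192.
- **That there is a four-week wash-out before follow-up.** This is one possible reading only. Section 2.4.1 speaks of twelve weeks of intervention, and no section says that training stops earlier.
- **That fifteen cycles contradicts the training count.** The pointer to the laboratory protocol makes a test count the likelier meaning.
- **That unequal practice between experts and non-experts is an error in the plan.** Section 2.3 states that experts keep their usual activity and adds: "The only addition to their regular routines will be the two Pilates skills". That is a declared design feature, not a contradiction.

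**Conclusion.** The duration is wrong as written. Section 2.4.1 assumes twelve weeks of intervention, and the programme that 2.3 relies on for the non-expert group covers eight. Weeks 9–12, a third of the stated period, have no programme. The exposure behind that group's pre-post comparison is 8 or 12 sessions, or 128 or 192 repetitions of each tested skill. It cannot be told from the article whether the follow-up measures status at the end of training or after an untrained interval.

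The repetition totals assume one session a week, as 2.3 states, full attendance, and that two series of 8 means 16 per session. The eight-versus-twelve conflict itself needs none of these assumptions. The repetition wording is a secondary matter of clarity, not a demonstrated contradiction. Nothing in the article shows which duration is intended, and this review does not choose.

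**What to change.** The sponsor must reconcile 2.3, 2.4.1 and Table A1 so that the length of the intervention, the weeks covered by the programme table and the timing of the follow-up measurement agree, and should state explicitly how the measurement is placed relative to the last training session.

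As secondary clarifications in the same edit:

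- say whether the eight and fifteen cycles in 2.3 are the laboratory test and, if so, separate them from the description of training;
- say whether the two series in Table A1 come on top of the 8 to 10 repetitions per station in 2.3 or are another way of describing them.

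The cost is a few lines of text, with no change to sample size, outcomes or analysis. It should be done before any follow-up measurement is taken, because the ambiguity cannot be repaired afterwards. A record of sessions attended would help interpretation, but it is optional, and a condensed article may leave it to the full protocol.
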